### Implementation {16c}

Research staff will enrol participants in each cluster. This will involve screening caregivers and their eligible child and consenting eligible and willing caregivers. Subsequently, baseline assessments will be conducted with consenting families in each cluster once the target number of caregivers is attained (i.e. 7–10). Then, a country-specific independent allocator will use the randomisation system to assign clusters to the intervention or control arm and inform a SPARK research staff member, who will inform participants of their allocation status.

## Assignment of interventions: masking

### Who will be masked {17a}

Independent allocators will assign clusters to the intervention or control arm using the bespoke randomisation system designed by the King’s College Trial Unit. As such, they will be unmasked to cluster allocations but will have no interactions with participants. The site-specific data managers will be unmasked to facilitate routine database checks but will have no access to research participants and will not summarise or analyse data. Data collectors will be masked to allocation: research participants will be asked to conceal their allocation from the data collector. Data collectors will be systematically asked following T1 and T2 assessments about any accidental unmasking. The primary outcome measures will be collected first to reduce the impact should data collectors be unmasked during data collection. Measures to be completed exclusively by participants in the intervention arm will be completed during the CST sessions to ensure outcome data collectors remain masked during trial assessment time points.

The trial statistician will be masked to participant allocation until the statistical analysis plan (SAP) has been finalised and signed. The senior statistician will remain masked throughout the trial but will be unmasked to complete final checks on the analysis code and statistical report after data have been collected, the database has been locked, analysed, and the first draft of the statistical report has been prepared. The principal investigators, co-investigators, and trial steering committee members will also remain masked throughout the trial, except in a serious adverse event (SAE) that necessitates revealing a participant or specific cluster’s allocation. The level of masking of the DSMB will be at their discretion, but they will likely see data split across multiple clusters at least at a partially masked (i.e. arms described as A/B) level. The Trial Steering Committee (TSC) will only be provided with an open report with pooled data that is not separated out by arm. In case of a major safety concern, the DSMB and TSC can request unmasking. Masking will be maintained across these team members by preventing interactions with research participants. Further, masked team members will not have access to the extracted randomisation list or data summarised across clusters.

### Procedure for unmasking if needed {17b}

If needed, we will first unmask the trial statistician. The unmasked statistician will inform the DSMB of sections of the report pertaining to the different arms. In case of a major safety concern, the DSMB and TSC can request unmasking.

## Data collection and management

### Plans for assessment and collection of outcomes {18a}

Primary and secondary outcome data will be collected by trained data collectors. Other data (e.g. process data, clinical data) will be collected by data collectors, research assistants, and, in some cases, the supervisors and non-specialist facilitators during the CST sessions in each site. Details on data accuracy checks and procedures are outlined in the section below and in the data management plan. The different types of measures and forms that will be used in this study are listed and described below.

#### Demographic and service history information survey

This survey was developed by our research team to collect demographic and service history information like the receipt of educational and health services related to the child, the caregiver, and their household.

#### Developmental and clinical assessment

We will record the outcome of the developmental and clinical assessment, noting the type and severity of DD and any co-occurring conditions.

#### Two primary outcome measures

The PEDsQL. The PEDsQL Family Impact module is a 36-item scale measuring the impact of a child’s condition on the family’s functioning across eight domains: caregiver’s physical, emotional, social, and cognitive functioning, communication and worry, and the family’s daily activities and family relationships. The PEDSQL acute version, which asks about the family’s quality of life over the past 7 days, will be used. This instrument was previously adapted and translated into Amharic and has good to excellent ratings on internal consistency and test–retest reliability (i.e. 0.80–0.96) on the total scores and almost all subscales, and good known group validity [24, 28].

The CBCL. The 99-item preschool and 113-item school-age versions of the CBCL will be used to assess the child’s internalising and externalising behaviours. Caregivers rate the veracity of statements on three levels: 0—not true, 1—somewhat or sometimes true, and 2—very true or often true. The CBCL has been translated into many languages and validated worldwide, including Amharic and Swahili. In previous studies, the translated Swahili version was found to have excellent Cronbach alpha internal consistency ratings of 0.96 [25, 46, 47].

#### Additional secondary outcome measures

In addition to assessing the co-primary outcomes at T2, further secondary outcome measures include the following:The adapted affiliate stigma scale. The 22-item questionnaire assesses caregivers’ self-stigmatisation based on their child’s disability, on a four-point scale (i.e. 1—strongly disagree, 2—disagree, 3—agree, and 4—strongly agree) [31]. It had excellent internal consistency rates (i.e. Cronbach’s *α* = 0.95 and 0.94) when used among caregivers of people with intellectual disability and mental illness, respectively [31].The adapted family interview schedule. A 14-item measure assessing caregiver’s community-based experience of stigma, previously adapted and tested in caregivers of children with DD by our research group in Ethiopia [30]. Items are rated on four levels: 0—not at all, 1—sometimes, 2—often, and 3—a lot. The adaptation targeting caregivers of children with developmental disabilities was found to have a Cronbach alpha internal consistency rating of 0.92 [30].The Patient Health Questionnaire, nine-item version (PHQ-9). The PHQ-9 comprises nine questions assessing caregiver’s depressive symptoms and has been translated and validated for use in Ethiopia and Kenya [33, 48, 49]. We will use the Ethiopian adaptation, which first probes the presence of each symptom using a dichotomous variable (i.e. yes or no) and subsequently asks about the weekly frequency if a ‘yes’ response was endorsed. The PHQ-9 has shown evidence of good construct and convergent validity in previous studies [33].The Household Food Insecurity Access Scale (HFIAS). The HFIAS is a 9-item caregiver-reported measure assessing problems regarding access to food within the caregiver’s household over a 4-week period [39, 50]. The HFIAS has been translated and validated in Amharic and Swahili. Studies assessing the validity of the Ethiopian adapted version indicate the tool has adequate validity (i.e. *α* ranging from 0.73 to 0.76 in different rounds of tests).UNICEF’s Multiple Indicator Cluster Survey (MICS) on child discipline [41]. The measure explores parents’ perceptions of the value of punishment in raising children and the types of punishment they adopt. It includes 10 questions assessed on a dichotomous scale (i.e. yes or no).The WHO CST knowledge and skills checklist. This was developed specifically for the CST intervention and assesses caregivers’ knowledge of the CST (24 items) and their confidence in applying its strategies in routine care (13 items). Although it has been used extensively in CST studies [15, 21, 22], it has not yet been formally validated. Our team has translated the tool into Amharic and Swahili and will validate the measure in the trial baseline data.The EQ-5D-5L. This is a standardised measure for assessing caregiver’s quality of life in terms of the degree of problems faced along five dimensions: mobility, self-care, usual activities, pain/discomfort, and anxiety/depression. The degree of problems may be rated as no, slight, moderate, severe, or extreme. The tool has been widely used internationally and has shown moderate to strong correlations with global health measures [51]. We will use the approved Amharic and Swahili versions.The EQ-5D-Y. This is a proxy measure of the EQ-5D-5L for assessing children and adolescents’ quality of life in similar domains as the EQ-5D-5L. Items are rated on three levels—no problems, some problems, and a lot of problems. An approved Amharic version of the tool does not yet exist. Therefore, we will only use the currently available Swahili version in Kenya.The Oslo social support survey (OSSS-3). The OSSS-3 comprises three items assessing caregiver-reported social support along three dimensions: the caregiver’s number of close confidants, their perceptions of people’s concerns, and the ease of obtaining practical assistance. The tool has been used in previous studies with Ethiopian communities [52].The adapted communication profile. Children’s communication mode and function will be assessed using two validated subscales of the adapted communication profile, originally developed for use in Kenya and Uganda [53] and subsequently adapted, translated, and validated for use in Ethiopia [44]. The 33 items comprising the validated subscales are measured on five levels ranging from 0—never to 4—always. These subscales have excellent validity and reliability in Ethiopia (Cronbach’s alpha = 0.97; kappa = 0.60–0.95, *p* < 0.001; ICC = 0.97, *p* < 0.001) [44].

#### Other measures—costing tools

Client service receipt inventory (CSRI). We adapted this measure to assess caregivers’ reported costs associated with caring for a child with DD in the Kenyan and Ethiopian context and to capture costs associated with care and education for children with DD and caregivers’ health-service-related costs. The costing tool has been pilot-tested in both countries and will be collected at baseline (T0), endpoint (T1), and follow-up (T2). In addition, we will assess the CST intervention-related costs in the intervention arm only through a brief survey administered during one CST group session and one home visit.

Provider-related costs. We developed an activity-based costing tool to assess provider-related costs associated with administering the intervention. These include staff, supervision, training, equipment, and travel costs. This tool tracks costs throughout the trial and includes start-up costs.

#### Other measures—CST materials

Developmental assessment-goal-setting. The goal-setting form was developed by WHO to assess the child’s developmental level, specifically communication and play, and inform the setting of developmentally appropriate targets.

Home visit attendance and records of the facilitator-child interaction. Caregivers’ attendance at home visits will be recorded by the research team to track adherence. In Ethiopia, we will also video-record the interactions between non-specialist facilitators and children during selected home visits. The recordings will be used in supervisory meetings to further coach and guide the efforts of non-specialist facilitators. Security and logistical challenges prevent recording of sessions in Kenya, where instead, supervisors will join the facilitator to attend a subset of the home visits.

Experience with caregiver interventions survey. We developed this survey to ascertain caregivers’ exposure to interventions for children with DDs and caregiver training materials relevant to DDs via parent support groups, friends or family, services (education, health, NGOs), online, radio or TV, or booklets. This survey is administered at the follow-up assessment to assess possible contamination affecting the trial.

The WHO CST Adult–Child Fidelity (FCI) rating scale. This scale, developed by the WHO CST team, will be used to assess the competency of non-specialist facilitators in applying the CST strategies during their interactions with children just after the trial’s start. It includes 12 items assessing mastery of the CST intervention strategies to promote communication, regulated behaviour, and skills learning. Items are rated on a 5-point scale ranging from 0 (‘strategy not demonstrated or inappropriately applied—needs substantial improvement’) to 4 (‘strategy applied appropriately at least 80% of the time—very good implementation’).

The adapted ENACT [23]. This measure will be used to assess the competency of non-specialist facilitators in delivering CST group sessions during the trial. This is an 18-item questionnaire [22] rated on a 4-point scale ranging from 1—needs improvement to 4—done well. The ENACT will be rated by trained CST supervisors during 3 out of 9 CST group sessions.

The Activity Completion Checklist (ACC). This tool measures the fidelity of non-specialists to the CST group sessions manual and was developed by our team during the Ethiopian pilot test. It indicates whether each activity in the session manual was fully, mostly, partly, or not completed. This checklist will also be rated by trained CST supervisors during 3 out of 9 CST group sessions.

CST group session attendance and home practice completion. We will maintain a record of caregivers’ attendance at the CST group sessions to ascertain adherence. Although we actively encourage only the consenting caregiver to participate in the CST sessions, we recognise that caregiving is socially distributed [54] and will record instances where there is a change in the caregiver attending specific CST sessions. Home practice completion will also be recorded during each group session.

In-depth interviews and focus group discussions. After all follow-up data collection is completed, focus group and in-depth interviews will be held with CST non-specialist facilitators, CST supervisors and master trainers, and caregivers. These topic guides explore how well the CST worked and consider contextual barriers and facilitators that may have influenced implementation, with a special focus on long-term sustainability. The full range of contextual determinants (informed by implementation science determinant frameworks), implementation outcomes, and process measures will be described in a separate implementation science protocol paper.

### Plans to promote participant retention and complete follow-up {18b}

We will promote participant retention by organising CST group sessions in central locations accessible to all group members. Guided by local research guidelines and practice, in Kenya participants will be compensated for research activity including travel time, will be given a refreshment/meal, and be compensated for out-of-pocket expenses and travel costs. In Ethiopia, participants will be given refreshments during all CST group sessions and will be reimbursed for travel costs.

If participants need to travel for collection of research data, they will be reimbursed for travel costs and compensated for time. If research data collection is at the participant’s home, they will receive an in-kind recognition of time burden (0.5 kg coffee in Ethiopia, dry food stuffs in Kenya).

Regardless of intervention adherence, the primary caregiver who completed the T0 assessment will be invited to participate in the T1 and T2 assessments. Likewise, caregivers in the control arm who are exposed to the CST intervention (through study error, trial contamination or due to exposure to the CST outside the trial) will remain in the trial control arm and will have their outcomes assessed.

### Data management {19}

The latest version of the Research Electronic Data Capture (REDCap) [55, 56] clinical data management system hosted at Addis Ababa University will be used in this trial. Data for the primary and secondary outcomes will be entered directly into REDCap as source data, with the exception of the EQ-5D measures, which stipulate paper and pen data collection and will be entered into REDCap immediately after data collection. Some process measures and key clinical information from the clinical verification assessment are collected on paper and subsequently entered in the electronic Case Report Form. Each site will have rights to access, view, download, and conduct routine internal checks on their site-specific data. Data entered from paper records entered in REDCap will be checked against the source data for accuracy. All data will be centrally stored and managed by the AAU trial team at the Clinical Trial Unit at the Centre for Innovative Drug Development and Therapeutic Trials for Africa (CDT-Africa). The AAU trial team will complete further checks based on the detailed data management plan. Data will be locked for analysis after all data have been entered, checks have been completed, and queries from audit checks, routine monitoring, and external audit checks have been addressed.

Paper source copies of process data will be stored for a minimum of 10 years in secure filing cabinets in each site’s project coordinator’s office. Other electronic data such as qualitative process data will be stored on encrypted project laptops and backed up on encrypted project hard drives and/or automatically on university servers at local sites. Pseudonymised qualitative data will be stored centrally in the project’s SharePoint data storage system: a GDPR-compliant file-sharing system managed by King’s College London and accessible to all collaborators.

### Confidentiality {27}

All research staff will be trained on the importance of ensuring participant and data confidentiality.

Participant consent will be carried out in private areas where they can comfortably consider participating without intrusion. However, the potential participant can consult with others before deciding to participate. Once enrolled, they can also object to participating in specific activities (e.g. video recordings) or withdraw from the study at any time.

All primary data collected in this project will be stored securely in the collecting institution following institution-specific data governance policies. All participating families will be assigned a caregiver-child dyad identification (ID) number. Data files will include only the ID code without any personal identifiable information. We will maintain a single master file per site linking caregiver-child dyad IDs with personal identifiers in a secure location in the in-country PI’s, trial coordinator’s, or data manager’s office. This file will not be stored centrally and will be maintained and updated by the in-country PI, site-specific trial coordinator, or data manager. The primary storage location for paper-based data will be a secure filing cabinet in the local site’s research office, and paper-based data with personal identifiers (e.g. consent forms) will be kept separate from questionnaire and interview data.

Electronic data will be collected using project-encrypted laptops and stored on the local site-specific servers and, subsequently, on the central server or network. In Ethiopia, external hard drives will also be used to back up electronic data regularly.

### Plans for collection, laboratory evaluation, and storage of biological specimens for genetic or molecular analysis in this trial/future use {33}

Not applicable, as we will not be collecting biological specimens.

## Statistical methods

### Statistical methods for primary and secondary outcomes {20a}

Primary and secondary outcome variables will be summarised using appropriate descriptive statistics (mean and standard deviation, median and interquartile range or frequency and proportion overall and by intervention arm at baseline (T0), and at endpoint (T1) (18 ± 2 weeks post-randomisation) and follow-up (T2) (44 ± 2 weeks post-randomisation)).

The primary analysis will be an individual-level analysis conducted using separate multilevel, mixed-effects linear regression models for each of the primary outcomes, with the two post-randomisation measures as dependent variables, and adjusting for baseline score, time point and country/site strata as fixed effects. Models will include an intervention arm-by-time point interaction to allow for different effects at T1 and T2, with the effect at T1 extracted as the primary outcome. It will also include pre-specified adjustments for the baseline variables child age, child sex, and caregiver education to reduce the impact of any imbalance of potential confounders at the individual level between arms. We will plot normality probability graphs of the residuals from the primary analysis models to assess the degree to which scales conform to model assumptions, with either normalising transformations applied or robust standard errors used where necessary. Tests of intervention effect homogeneity by country will be presented. If the country effect is significant, we will subsequently assess intervention effect homogeneity by site (urban vs rural) within country. The administration of two different CBCL questionnaires to children of different ages will be handled by estimating Cohen’s *d* effects for the questionnaires separately, using the baseline standard deviation in each case, and then combining the two Cohen’s *d* estimates together as a weighted average with an appropriate confidence interval.

We will use similar methods to analyse the secondary outcomes. The main secondary outcomes will be the intervention effect on PEDsQL and CBCL at T2, extracted from the models described for the primary outcomes. All other secondary outcomes are also continuous variables and will be analysed using similar models, using the T1 intervention effect extracted for each secondary outcome. A detailed statistical analysis plan will be drafted and approved by the DSMB.

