One of the few studies conducting a randomised controlled trial design was a Pakistan-based effectiveness evaluation of a heavily adapted version of the CST intervention based on a preliminary field-testing draft. It excluded all individualised components and was delivered with other components of the WHO’s Mental Health Gap Action Programme (mhGAP) through a tablet application. Five hundred and forty parents of 2–12-year-old children with DDs participated in the intervention, delivered by trained family volunteers. Its results were less positive: compared to the control arm, caregivers in the intervention arm reported greater health-related quality of life, but no significant differences between arms were found on the primary outcome measure, child functioning, or any other secondary outcome measure examined [18]. The authors attributed the non-significant findings to the heterogeneity of the sample and the relatively short intervention timeframe, which was about 3 weeks shorter than originally planned. Additionally, the substantial adaptations to the intervention itself, which drastically simplified its contents to improve contextual fit and potential scalability, may also have contributed to the non-significant findings.

In contrast, our team in Kenya conducted a pilot study including a control group and found the CST to be effective at reducing children’s internalising and externalising challenging behaviours and caregivers’ stress and depressive symptoms in the intervention arm compared to the control arm [12]. There were also significant improvements in caregivers’ quality of life, favouring the intervention arm.

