Additionally, in a randomised controlled trial from Italy of CST against enhanced treatment-as-usual, Salomone and colleagues [19] found that participating in the CST intervention delivered by specialist facilitators in public health settings was associated with significant improvements in the masked-rated primary outcomes assessing caregivers’ skills in supporting joint engagement with their child, and the dyadic fluency of the caregiver-child interaction, compared to caregivers in an enhanced treatment-as-usual control arm, who received a single psycho-education session. Significant treatment effects were also reported for caregiver self-efficacy, stress, and child gestures. A sequential mediation analysis testing the theory of change indicated that changes in caregiver’s skills significantly mediated the effect of treatment at the 3-month follow-up on the dyad primary outcome and the other child outcomes [20].

In summary, preliminary findings from pilot studies and RCTs of the CST (or versions thereof) have been largely promising despite some non-significant findings from specific studies. However, many of these studies have been limited by factors such as small sample sizes [13, 17, 21], a narrow focus on children with autism instead of children with a wider range of DDs [18], and limited implementation in LMIC contexts, where most children with DDs reside. Moreover, many studies evaluated the intervention using specialist-based intervention delivery instead of delivery by non-specialists [17, 21, 22]. The effectiveness of the revised CST has not yet been fully examined among caregivers of children with a wider range of DDs where a task-sharing model employing non-specialist facilitators has been adopted. This protocol paper outlines plans for conducting a 2-arm assessor masked hybrid type-1 effectiveness implementation parallel cluster randomised controlled superiority trial (RCT) to test the effectiveness and the resource impacts and costs and consequences of the CST in four sites in urban and rural Ethiopia and Kenya. We use a cluster design because the intervention is delivered to groups of caregivers.

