### Methods for additional analyses (e.g. subgroup analyses) {20b}

We will carry out exploratory pre-specified analyses to determine whether specific baseline moderators, i.e. (a) caregiver educational level; and (b) social support, modify the intervention’s effect on children’s behavioural problems (CBCL) and caregivers’ quality of life (PEDsQL) at T1 and T2.

We will also assess mediational and post-randomisation moderator effects, which will not be reported in the main trial paper. The mediational analysis will use the interventional in(direct) effects approach [57] that permits simultaneously accounting for post-randomisation moderators and multiple mediators. With it, we can investigate the extent to which the intervention induced change in caregiver quality of life by changing child behavioural problems (our main mediator). The method will also reveal how several indirect effects contributed to the intervention’s total effect. We plan to investigate the following: (i) the indirect effect of the intervention on change in child behavioural problems; (ii) the indirect effects through post-randomisation moderator factors such as the number of CST sessions attended, fidelity of CST group sessions and competence of the CST facilitator, and home practice completed; and (iii) the indirect effects of the intervention through other potential mediators such as social support, caregiver perceived stigma, and physical punishment.

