### Methods in analysis to handle protocol non-adherence and any statistical methods to handle missing data {20c}

Our power and sample size calculations account for missing data based on realistic patterns of dropout over repeated measurements. We will produce frequency reports of participants who purposefully withdraw from the trial or are passively lost to follow-up by site and arm at 18 ± 2 weeks post-randomisation (T1) and 44 ± 2 weeks post-randomisation (T2).

We will use intention to treat principles that analyse participants within their randomised clusters, with mixed effects models including participants with at least one outcome measure, assuming data are missing-at-random. Our analyses will also include any baseline variables found to be associated with missing outcome data in models to make the missing-at-random assumption more plausible.

Moreover, if attrition rates exceed the levels assumed in the power calculation, we will compute a sensitivity analysis that will impute missing-data values under two scenarios: (i) outcomes remain unchanged from or return to baseline and (ii) where attrition in the control arm is related to improvement of 0.1 SD and in the active arm is related to a worsening of 0.1 SD [58, 59].

We define adherence as the family participating in at least 7 group sessions and 2 home visits, and if we register non-adherence rates of 10% or more, we will do a complier average causal effect (CACE) analysis for the two primary outcomes [59, 60] as a more principled version of a per-protocol analysis. We will compare those who complied/were adherent in the intervention arm with those in the control arm who would have been adherent if they had been allocated to the intervention arm. The CACE will be obtained using instrumental variable methods [60] with the primary outcome of interest as the dependent variable and adjusting for similar variables to those described for the primary intention to treat analysis. If we later find any individuals were ineligible and mistakenly entered into the trial, we may redo the CACE analysis with these individuals removed.

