## Appendix

**Table 2 Tabb:** Participant timeline

	**Clinical assessment (by specialist clinician)**	**Study information and screening (by research staff)**	**T0, baseline assessment (pre-randomisation; by independent data collector)**	**Randomisation**	**CST home visit 1, 2, 3 (by CST non-specialist facilitators)**	**CST group session 1, 2, 3, 4, 5, 6, 7, 8, 9 (by CST non-specialist facilitators)**	**T1, endpoint assessment (by independent data collector)**	**T2, follow-up assessment (by independent data collector)**	**Qualitative assessment (by independent researcher)**
**Study week**	≈ − 5	≈ − 5 to − 2	− 2 to − 1	0	2; 8; 13	3–7; 9–12	18 ± 2 weeks	44 ± 2 weeks	Week 46–58

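### Type of developmental disability is recorded before randomisation but is neither a named covariate nor a pre-specified moderator, so no planned analysis asks whether the CST effect varies across the diagnoses enrolled

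*Protocol article*

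**What the plan says.** All references are to the protocol article; the SAP is not shown.

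- **Covariates.** Section {20a} sets up mixed models "adjusting for baseline score, time point and country/site strata as fixed effects" and adds "pre-specified adjustments for the baseline variables child age, child sex, and caregiver education". The stated purpose is to limit the effect of chance imbalance in possible confounders. Section {20c} adds a data-driven element: "Our analyses will also include any baseline variables found to be associated with missing outcome data in models".
- **Moderators.** Section {20b} plans exploratory analyses of "specific baseline moderators, i.e. (a) caregiver educational level; and (b) social support", for both co-primary outcomes at T1 and T2. Section {12} says these will appear in the main trial paper. Section {20a} also tests homogeneity of effect by country and, if that is significant, by site within country.
- **What is measured.** The section on developmental and clinical assessment records its outcome, "noting the type and severity of DD and any co-occurring conditions". The Appendix timeline puts this specialist assessment at about week −5, with randomisation at week 0.
- **Rationale.** Section {6a} states the gap: "The effectiveness of the revised CST has not yet been fully examined among caregivers of children with a wider range of DDs", in a setting of non-specialist delivery. On the earlier trial in Pakistan it says: "The authors attributed the non-significant findings to the heterogeneity of the sample", and gives further reasons as well. Section {7} promises to examine whether impact differs by baseline variables that matter. Section {10} admits children with autism, intellectual disability or global delay, or certain communication disorders, singly or combined. It excludes some other diagnoses because the strategies fit their needs poorly.

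**The concern.** The protocol treats diagnosis as relevant to benefit when it sets eligibility, and cites diagnostic breadth as part of the reason for the trial. It then pre-specifies two moderators, both caregiver characteristics, and leaves out the child's diagnosis although it is already in hand. Against this text, a later analysis by DD type would be post hoc, whatever it showed.

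Two things are at stake. If the effect differs by diagnosis, the pooled estimate averages over the difference and no planned analysis describes it. And if DD type predicts outcome beyond the baseline score, the co-primary models forgo some precision.

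**Working it through.** **Inputs from section {14}:** alpha 0.025 per co-primary; effects 0.40 and 0.32 SD; mean cluster size 8.5; 10% dropout by T1; ICC 0.05 in the intervention arm; 14 clusters per site for the power figure, raised to 16. Section {8} gives 1:1 allocation.

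**Assumptions, not in the documents:** two-sided tests; baseline–outcome correlation r; control-arm ICC of 0; share of residual variance explained by DD type and severity (R²); share p of a DD group.

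**1. The plan's own figures.** 56 × 8.5 = 476 and 64 × 8.5 = 544, as stated. For power, the analysed cluster size is 8.5 × 0.9 = 7.65, so the design effect is 1 + 6.65 × 0.05 = 1.3325 in the intervention arm and 1 in control. With 28 clusters per arm and r = 0.3:

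SE = √[0.91 × (1.3325 + 1) / (28 × 7.65)] = 0.0995

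Power = Φ(d/SE − 2.241) = 96.2% at 0.40 and 83.5% at 0.32, against the stated 96% and 83%. With r = 0 it is 94.4% and 79.5%. With ICC 0.05 in both arms and r = 0.4 it is 95.3% and 81.3%. The stated power therefore reproduces with a modest baseline correlation and does not rely on DD type.

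**2. Precision forgone.** Multiply the SE by √(1 − R²); effect 0.32, r = 0.3:

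| R² | Power, 56 clusters | Power, 64 clusters |
|---|---|---|
| 0 | 83.5% | 88.4% |
| 2% | 84.3% | 89.1% |
| 5% | 85.5% | 90.1% |
| 10% | 87.4% | 91.6% |

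The gain is 0.8 to 3.9 points at 56 clusters and 0.7 to 3.2 points at the planned 64.

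**3. What a DD-type interaction could detect.** Take a two-way split and 64 clusters, so 64 × 7.65 = 489.6 children analysed:

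SE = √[(1 − r²) × (4/489.6) × (1/p + 1/(1 − p))]

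The detectable difference is 2.80 × SE (80% power, 5% two-sided). For p = 0.5 it is 0.51 SD at r = 0 and 0.46 at r = 0.4. For p = 0.3 it is 0.55 and 0.51. A variant with 245 per arm, a factor 1 − ICC = 0.95, p from 0.2 to 0.5 and r from 0.3 to 0.44 gives SEs of 0.158 to 0.210, hence 0.44 to 0.59 SD. Roughly 0.45 to 0.6 SD covers both. Three diagnostic groups would do worse than a two-way split.

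**4. Illustration of dilution.** An effect of 0.4 SD confined to half the children averages 0.5 × 0.4 = 0.20 SD. The SE implied by the stated 83% is 0.32/(2.241 + 0.954) = 0.100 at 56 clusters, and 0.100 × √(56/64) = 0.0937 at 64. Power for the overall effect is Φ(0.20/0.0937 − 2.241), about 46%. The difference between halves, 0.4 SD, lies below the 0.46 to 0.51 SD that step 3 gives for an even split, so the interaction test would have less than 80% power too.

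**The case against.** The choices are coherent as they stand. The primary objective is the overall effect, and enrolling a broad population and estimating that effect already addresses the stated gap. A short list of low-power interactions is defensible, and the unseen SAP may name DD type.

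Several stronger readings are tempting, and the documents do not support them:

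- *That the covariate list is closed.* Section {20c} adds baseline variables associated with missingness. This could admit DD type or severity, though only by chance.
- *That chance imbalance in diagnosis biases the co-primary estimates.* For a DD feature with assumed prevalence 30 to 50% and ICC 0 to 0.10, the 95% range of the difference between arms is about ±8 to ±11 percentage points. This is sampling error: zero in expectation under randomisation and already in the standard error. The baseline score also carries part of any severity effect.
- *That the earlier trial failed because of mixed diagnoses.* Section {6a} also cites a shortened intervention and heavy adaptation, and does not equate heterogeneity with DD type.
- *That the trial cannot examine variation by diagnosis, or that an added moderator would rescue a diluted result.* The data will exist, so exploratory work remains possible; step 4 shows the interaction would itself be underpowered.

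On practicality, section {10} allows several diagnoses per child, and no common severity scale is described.

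These objections limit the point without removing it. The two moderators already listed are exploratory too, so low power does not explain why diagnosis was left out.

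**Conclusion.** The point holds as a gap in a stated list. DD type is available before randomisation and bears on the trial's rationale and eligibility rules, but it is in neither the named adjustments nor the two moderators. The overall effect estimate is valid without it.

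The main loss is the absence of any pre-specified analysis of whether the effect varies across the diagnoses enrolled. The lesser loss is about 1 to 4 points of power. That rests on the assumed R² of 2 to 10%, for which the documents give no figure; r, the control-arm ICC and the DD shares are assumed as well. The value of the added analysis lies in reported estimates with confidence intervals. It would not be a decisive test.

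**What to change.** Before the trial statistician is unmasked, which under section {17a} means before the SAP is signed:

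1. In {20b}, add DD type to the pre-specified exploratory moderators, with a rule fixed in advance for children with more than one diagnosis. Report arm-by-type estimates with confidence intervals in the main paper, labelled exploratory, with the detectable difference of roughly 0.45 to 0.6 SD stated.
2. In {20a}, add DD type to the fixed covariates of the co-primary models.
3. Add severity to either list only if it is rated on one scale comparable across diagnoses.

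If the SAP already does this, align the protocol text with it; if DD type was left out deliberately, say why.

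The cost is a wording change, a classification rule that needs clinical agreement, and a few model terms. It needs no new data, visits or families. The downside is a few degrees of freedom and one more low-power interaction.
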